### Psychological Tasks (= computer-based activities)

|                     |                                                                                                                                                                                                                                                 |          |
|---------------------|-------------------------------------------------------------------------------------------------------------------------------------------------------------------------------------------------------------------------------------------------|----------|
| Self-reference task | Participants are asked to respond to prompts on the computer screen during fMRI scanning about the personality attributes of themselves, close friends, and strangers by pressing buttons to indicate yes, no, or how much a statement is true. | ~ 15 min |
| Transitions task    | Participants are asked to respond to questions about their own and other people's mood and changes in mood. This task is done outside of the scanner.                                                                                           | ~20 min  |

### Safety / Risk Assessment

#### *Oversight of risk assessment and response*

Overall risk will be managed by [name] in consultation with [name] (site PI at U Mass), and the MGH study clinician. The study team will meet regularly (at least every two weeks) to review recruitment and risk management.

*Risk assessment plans built into scheduled study procedures*

- **Safety plans:** Each patient will work with study staff to complete a safety plan at the beginning of the study with either clinical assessment team or DBT team using a standard approach (Brown and Stanley method). This safety plan includes specific plans for thoughts and behaviors to do if risk level is low, moderate, or at crisis level. For example, something to do if risk is low could be to practice mindfulness meditation. Something to do if risk is moderate could be to leave an upsetting situation. Something to do if risk is at crisis level could be to call 988 for support or call a helpful friend to come over to provide support. The plan includes specific contact details for resources, including both those suggested by the participant during the safety planning conversation that results in the written plan, and also including a standard set of local and national resources included in every plan (988, crisis text line, local resources for New Haven or Boston depending on the participant's location). Once made, the plan resides in REDCap to help study staff support participants as needed throughout the study, and is emailed to the participant right away, and again as needed to allow them to use it and to share it with their support system. Participants are encouraged to view the safety plan as a living document and to ask study staff to update it anytime. We encourage participants to keep a paper copy with them (in their wallet or similar). If participants don't have easy access to a printer, study staff will offer to send it in the mail or bring it to the scanning day, depending on participant preference.
- **Risk assessment tool 1: UWRAP** In addition to the safety plan, the risk assessment tool (UWRAP) will be introduced at baseline to help participants become familiar with it and to assess baseline risk. This tool assesses distressing emotions and urges for dangerous behaviors on a 7 point Likert scale. At the end of each clinical assessment timepoint, as well as on an as-needed basis throughout the study, risk will be re-assessed with the UWRAP tool. If a participant endorses a 4 or greater for any item, further discussion of the situation will occur, and the participant will be offered a number of supportive activities from the UWRAP list and based on their personalized safety plan. Then risk will be assessed again using the scale.
- **Risk assessment tool 2: CSSRS** We will also assess suicidal ideation and behavior formally at each clinical assessment timepoint (baseline, after NF, at the start of each DBT mindfulness module, and at follow-up months 1 and 2) using the C-SSRS.
- **Risk assessment through staff/participant interaction** [name] lab staff and DBT program staff may also become aware of subject distress or symptom exacerbation, including suicidal ideation.

*Risk assessment by clinical study staff when risk is detected*

What will trigger study staff to immediately involve a study clinician for further assessment:

- Participant who is unable to participate in making a detailed safety plan
- Participant who endorses 4+ on any UWRAP item and level does not decrease below 4 after using UWRAP-suggested or safety plan-suggested behaviors
- Participant who endorses of type 4 or 5 ideation (suicidal ideation with intent or plan) or new suicidal behavior
- Any study staff concern that the staff member would like support in addressing

What study clinicians will do when contacted about risk:

Each study site has local study clinicians assigned to support risk management. Risks identified in the course of study recruitment (to be conducted by the Yale site staff) or the in-person mbNF day at Yale will be reported to [name]. Risks identified in the course of the in-person mbNF day at MGH will be reported to the on-call study clinician (to be named) during the visit. Risks identified in the course of remote DBT will be reported to [name] according to standard practice for this clinic. [name] directs an active remote DBT skills group at UMass with weekly groups running according to the model that we plan for this grant. She now has several years' experience with risk management in remote DBTsg, and is prepared to manage risk. She has an active psychology license in Massachusetts and Connecticut.

Any time that study staff would like clinical support or a participant meets one of the criteria listed above, local clinical study clinician will be immediately contacted to discuss the situation and if needed to assess the participant.

Clinical assessments by study clinicians may include review of the participant's thoughts and behaviors in the context of their clinical history to understand current risk of harm to self or others, collaborative review and use of the personal safety plan with the participant, development of immediate next steps including planning strategies to reduce distress and risk, contacting helpful others (friends/family/mental healthcare providers), and if needed, contacting emergency services for further assessment and potential transfer to the emergency department. If emergency services are needed, clinical staff and the local study clinician will make every effort to keep the participant in the visit until the emergency services arrive to ensure safe transfer to their care.

Please refer to section 5.1.2. below for details about reporting of adverse events.

**Randomization and control condition**

Subjects assigned to receive NF at each site (Yale and MGH) will be randomized within-site using a predetermined randomization schedule prepared and known only to the site neuroimaging staff (the rest of the study staff will remain blinded). Each schedule will result in 1:1 randomization with the constraint that the number of mbNF cases is always  $\geq$  the number of control-NF cases (necessary to ensure each control subject has a prior mbNF subject to be matched to) and also the constraint that the number of mbNF cases does not exceed the number of control-NF cases by more than three (to keep the two groups reasonably balanced over time). Clinical staff and assessment raters will remain blind to group assignment. Subjects will be debriefed at the end of the study and at that time their group assignment will be disclosed.

**Yoked-sham feedback** Subjects in the control-NF group will complete the mindfulness training and undergo similar MRI scan procedures. The primary difference in scans is that the control-NF subjects will not receive feedback based on their own brain's activity but will receive feedback based on data extracted from a previously-acquired mbNF session with a different study subject. Thus, the visual display will be independent from the subject's own brain activity in the control-NF group. This ensures that subjects across groups are viewing equivalent stimuli. This yoked sham control approach was chosen for this study because it allows for subject blinding, creates a similarly engaging feedback training experience, and balances positive feedback received across groups. Specifically, a control-NF subject receives feedback indicating they are having the same amount of success as the NF subject they are yoked to. The perception of success can impact motivation because it is easier to stay motivated if the participant feels they are having some success. It is also likely to affect

the magnitude of the placebo effect, because if a participant sees that they are successful in controlling their mindfulness-related brain patterns, they are likely to have a larger placebo effect. Thus, controlling for perception of success is critical.

An alternate control used for some studies involves training subjects to control a different brain region that is unrelated to their symptoms. This approach has the disadvantage that success in controlling the region may be significantly different in the control and NF groups, as some brain areas are more easily controlled than others, leading to different perceptions of success on the task and thus differences across groups in both motivation and placebo effects. That being said, one concern that applies to all sham-controlled studies is that subjects in the control group may notice that the feedback does not track with their emotional state, which could damage the blind. For this reason, we will include a debriefing session at the end of our study when we will ask subjects their beliefs about their group assignment (which intervention they think they received, and how confident they are about their group assignment). Subjects and clinical study staff will be blinded to randomization to ensure that the experience of the two groups is as similar as possible. Overall, by providing maximally similar procedures for the mbNF group and the control-NF group, we aim to account for potential mindfulness practice effects (e.g., learning, utilization) and non-specific scanner effects. At each subject's study completion, we will unblind. We will first debrief the subject, and then tell them if they got mbNF or control. We will monitor their affect and, for any subjects who are upset upon learning their group assignment, clinicians will be available to help assess and support them as needed.

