#### 4.3.1 Number of Participants

124 completers, plus up to 20 additional mbNF pilot participants (10 in New Haven, 10 in Boston), who will not undergo psychotherapy. (If participants dropout mid-study, we may replace them).

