## **Neurofeedback Day (mbNF or control NF)**

### ***Mental Noting training***

After the baseline resting state scan, subjects will learn a “mental noting” mindfulness practice to use during the neurofeedback scans. Trained research staff will provide this semi-structured 45-minute training established in our prior work. Mental noting is a major component of Vipassana (insight mindfulness meditation); key principles include “concentration”, “observing sensory experience”, “not ‘efforting’”, and “contentment”. Subjects will be taught to mentally label/note whatever sensation is most prominent in their sensory experience from moment to moment (e.g., seeing, hearing, feeling, thinking). This practice primarily trains the “attention and control” mindfulness components, but also influences “attitude” by recognizing that “one’s thoughts and feelings are temporary, objective events in the mind, as opposed to reflections of the self that are necessarily true”, sometimes referred to as “decentering”. Training also will include identifying personal scenarios in which mental noting could be applied, explaining the goal of using these strategies to manage distress in daily experiences. Before the MRI scan, subjects will practice mental noting practice by verbalizing their mental label out loud to the study staff, who will observe the practice and provide feedback as needed. Subjects will then complete a silent practice of mental noting while viewing a simulation of neurofeedback. All subjects will be trained until they feel competent to use mental noting in the scanner. During mbNF (6 runs, 2.5 mins each), subjects will use mental noting with the aim of controlling the visual feedback; specifically, they will try to move the position of the white dot toward the (upper) red circle and away from the (lower) blue circle (**Fig 1**).

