Roles and Responsibilities: [name], [name], and the Yale Human Research Protection Program (HRPP) will work together to monitor the safety of subjects at the Yale site. Yale will serve as the single IRB for the whole study. [name] and MGH clinician [name] MSW will monitor the safety of subjects during in-person scan days at the MGH site, and remain in close contact with the whole leadership team about any concerns. [name] team at U Mass Amherst will see the study subjects in remote DBT skills group each week and will raise any concerns with the rest of the study leadership team. In addition to day-to-day oversight, [name] will formally review all the clinical assessments on a quarterly basis to identify any potentially concerning patterns. The clinical raters and therapy teams will be blinded to subject group (mbNF or shamNF), but the neurofeedback staff ([name], [name] and the at-scanner research assistants) will not be blinded, so they will review the study data quarterly as well to identify any potentially concerning patterns by group. A DSMB will be constituted by the study leadership team in consultation with the Program Officer in order to ensure that people with expertise in BPD and clinical trials are at the table. The study leadership team (Drs. [name], and as needed, Drs. [name], [name], [name], and [name]) will meet with the DSMB every six months to review all clinical data and discuss any potential clinical safety issues. The study staff that collect adverse events information will report serious and adverse events and UPIRSOs immediately to [name] who will review them to determine if further action is necessary. If there is any doubt, they will be discussed with the DSMB and IRB and officially reported and handled as recommended.

Any unanticipated or serious adverse events will be reported immediately to [name] who will report them to the NIH as required. Unanticipated or serious events will also be discussed immediately by [name] and [name], including the rest of the leadership team as needed, to assess their likelihood of being related to the intervention and to determine, in consultation with the IRB, if the study protocol should be modified or stopped.

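### The allocation list is made and held by the unblinded imaging staff, with nothing to delay release of the arm until after the pre-NF scan and training, and the one-sided balance rule lets enrolment order predict the arm.

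*Protocol*

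**What the plan says.** **Who makes and holds the list.** Section 5.1, Randomization and control condition, sets a predetermined schedule within each site, "prepared and known only to the site neuroimaging staff". All other study staff are to stay blinded.

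**The rule.** "Each schedule will result in 1:1 randomization", under two limits. The mbNF count may never be below the control count, which is called "necessary to ensure each control subject has a prior mbNF subject to be matched to". The second limit, given for balance over time, is that "the number of mbNF cases does not exceed the number of control-NF cases by more than three".

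**Who is unblinded.** Section 6.5, Roles and Responsibilities, says that the neurofeedback staff, including the research assistants at the scanner, "will not be blinded, so they will review the study data quarterly as well to identify any potentially concerning patterns by group". Clinical raters and therapists are blinded.

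**Order of the neurofeedback day.** The pre-NF resting scan comes first, then mental-noting training, then the feedback runs. The training is semi-structured and nominally 45 minutes, but "All subjects will be trained until they feel competent to use mental noting in the scanner". Under Minimizing MRI Data Loss, a resting run can be lengthened in real time to gather enough low-motion data.

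**Pilot sessions.** Section 4.3.1 plans "up to 20 additional mbNF pilot participants (10 in New Haven, 10 in Boston), who will not undergo psychotherapy".

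**The concern.** In a yoked-sham trial someone at the scanner must know whether to load live or replayed feedback. That person need not know the arm before the feedback runs, and need not hold the list of all future arms. The protocol allows both.

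The steps before feedback involve judgement: how long to train, how much encouragement to give, whether to lengthen the resting run, and what to say about head motion between runs. If these differ by arm, the change in connectivity from pre- to post-NF can differ for reasons other than the feedback. That change is a primary outcome (Section 4.2.1) and the go/no-go criterion (Section 5.4.3). BSL23 is exposed less directly: blinded participants report it, and its primary endpoint is DBT week 16, after therapy from blinded therapists.

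The second issue reaches staff who never see the list. A limit that binds on one side only makes the arm depend on position in the enrolment sequence. Recruitment, consent and assessments all sit with Yale staff (Section 4.1.3), and Section 4.3.2 permits exclusion at the discretion of the study PI.

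**Working it through.** **Inputs.** Allocation is 1:1 within site. Let D be mbNF minus control at a site; D must stay in {0, 1, 2, 3} (Section 5.1). There are 124 completers at two scanning sites (Section 4.3.2), attrition is about 30% (Section 5.4.1), and the interim analysis has 26 per group (Section 5.4.3). The protocol does not say how draws are made between the limits, so two assumptions are shown.

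**The plan's own figure.** 124 / 2 sites / 2 arms = 31 per arm per site, as stated. Allowing for attrition, 124 / (1 - 0.30) = 177.1, so 178 randomised, or 89 per site.

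**Assumption A: a fair draw whenever both arms are allowed.**

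- D = 0 forces mbNF, and D = 3 forces control.
- Long-run probabilities of D = 0, 1, 2, 3 are 1/6, 1/3, 1/3, 1/6. Forced share = 1/6 + 1/6 = 1/3.
- For finite lists the forced share is 35.0% at 26 per site, 34.1% at 62 and 33.8% at 89.

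The chance of mbNF at a given position is P(D=0) + ½[P(D=1) + P(D=2)]:

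| Position | State before the draw | P(mbNF) |
|---|---|---|
| 1 | D = 0 | 1.00 |
| 2 | D = 1 | 0.50 |
| 3 | D = 0 or 2, each ½ | ½·1 + ½·½ = 0.75 |
| 4 | D = 1 (¾) or 3 (¼) | ¾·½ + ¼·0 = 0.375 |
| Later odd | D = 0 (1/3) or 2 (2/3) | 1/3 + 2/3·½ = 2/3 |
| Later even | D = 1 (2/3) or 3 (1/3) | 2/3·½ = 1/3 |

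Guessing mbNF at odd and control at even positions is right about 67% of the time over 62 participants.

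**Assumption B: every admissible 62-person sequence ending 31:31 is equally likely.** The forced share is 28.2% at the limits, or 30.8% counting assignments fixed by the end of the list. The mean chance of mbNF is 0.56 at odd and 0.44 at even positions, and guessing from order alone is right about 57% of the time. The first case is still certainly mbNF.

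**Comparison with permuted blocks.** A block of size b forces a share 1/(b/2 + 1): 33% for size 4, 25% for size 6, and about 28% for a random mix of the two. Someone who sees running counts guesses right as follows:

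- current rule, fair draws: 0.34 + 0.66/2 = 67%;
- current rule, equally likely sequences: 73%;
- random blocks of 4 and 6: about 69%.

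So blocks do not clearly beat the present rule against someone tracking counts. Their gain is that each position has probability ½, so order alone gives 50%.

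**Donor supply under blocks.** Within a block of size b, controls can lead by at most b/2, and the lead returns to zero at the block's end. For sizes 4 and 6 the maximum is 3, so three earlier mbNF sessions per site suffice even if no donor is used twice. The same bound keeps mbNF from leading by more than 3, which preserves the purpose of the cap.

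**The case against.** Several stronger readings are tempting, and the document does not support them.

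- **That forcing a third of assignments is the flaw.** Blocks of 4 force the same share, and whoever holds the list knows every arm, forced or not. Others lack running counts, because assignment is disclosed only at each participant's completion. What remains is predictability from order, which needs no counts.
- **That the pilots already make the lower bound unnecessary.** Section 4.3.1 gives a maximum number. It does not say the pilots finish first, can be used as donors, or are meant for yoking. They have no bearing on the upper limit, which serves balance.
- **That the quarterly by-group review should move to the DSMB.** That review looks for safety signals in a population with raised self-harm risk, and the DSMB meets only every six months. This point asks for no change there.
- **That the list-holders and the session staff are stated to be the same people.** The protocol uses two labels. The identity is a close inference, since someone at the scanner must load the right feedback. Who schedules sessions is not stated.

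Real safeguards also exist. Participants, raters and therapists are blinded. Training follows an established semi-structured format, and Section 6.6 requires staff to be trained to adherence in delivering it. These narrow the exposure. They do not close it, because no rule keeps the trainer or the operator of the pre-NF scan from knowing the arm.

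**Conclusion.** The point holds as a weakness in concealment. The full schedule is made and known in advance by imaging staff who are, by close inference, unblinded and present on the neurofeedback day, and nothing delays release until the discretionary steps before feedback are done. No bias is shown to have occurred and its size cannot be computed; this is preventable exposure, chiefly of the connectivity outcome and the go/no-go decision.

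The one-sided bound adds a measurable weakness. The first arm at each site is certain, and order alone predicts the arm about 57 to 67% of the time against 50% for a symmetric scheme. That range rests on the two assumptions about how draws are made, which the protocol leaves open. The change should be made; it does not call the design itself into question.

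**What to change.** 1. Have the site-stratified list generated by someone who runs no sessions, and hold it concealed in REDCap.
2. Release each assignment to the scanner operator only after the pre-NF surveys, the pre-NF resting scan and the mental-noting training. The existing order of the day allows this, because training precedes the feedback runs. The post-NF scan would still be run by someone who knows the arm.
3. If at least three usable mbNF pilot sessions per site are completed first and can serve as yoking donors, replace the one-sided bound with concealed permuted blocks of random size 4 and 6. Otherwise keep the bound.

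Cost: a protocol amendment and REDCap set-up, with no extra participants or scans. The first few controls at each site may be yoked to pilot sessions, whose level of success could differ somewhat from that of trial participants.

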### **Baseline (and Follow-up) MRI scans**

We will collect structural and functional MRI scans for participants at their local site (Yale for New Haven area participants, MGH for Boston area participants). We will collect these scans on neurofeedback day, and again at psychotherapy week 16 and at the two month timepoint after the end of psychotherapy. People capable of pregnancy will be offered a voluntary pregnancy test prior to each scan.

A member of the research team will accompany subject to the MRRC and will stay with the subject for the duration of the MR study.

At both sites, images will be acquired with 3.0 Tesla Siemens scanners equipped with a 64-channel head coil and integrated with our real-time fMRI analysis system. We will instruct subjects to minimize head and body motion during scanning, and will continuously monitor head motion online and provide feedback to subjects between scan runs if they move excessively.

MR imaging of the brain will be done, with or without performing a specific task. We may also complete MR imaging of the brain to record the diffusion tensor data. This data can be used to map out fiber tracks in the brain. We may also complete MR spectroscopy of specific brain areas to determine the chemical composition of those brain areas. This data is relevant to the density of neurotransmitters, for example. We will use a standard single-voxel sequence like STEAM or PRESS, for example, that is within the FDA power guidelines for power deposition.

During MR scans, recordings may be taken of the subjects' pulse (via a pulse-oximeter placed on their finger), respiration (via a pneumatic belt), and galvanic skin response (via sensors on the fingers) that are components of Siemens Physiologic Monitoring Unit. We may also monitor the subject's eye movements and/or pupil dilation using a camera and an eye-tracking system. This equipment is designed to be completely MR compatible. The records of pulse and respiration will be used during data processing to remove physiologic noise from the images.

**Minimizing MRI Data Loss** We will use an online tool that allows monitoring of structural data quality and immediate re-collection as needed. Framewise Integrated Real-time MRI Monitoring (FIRMM) allows for monitoring of head motion artifacts and a real-time extension of resting state run length to ensure sufficient low-motion data for analysis, which greatly reduces imaging data loss due to movement.

**Anatomical image acquisition** A high resolution, multi-echo (T1-weighted) structural image will be acquired during study baseline sessions for fMRI co-registration. The pulse sequence parameters will be: TR=2.530 ms, TE1=1.64ms, TE2=3.5ms, TE3=5.36ms, TE4=7.22ms, Flip =7°, field of view = 256cm, 1 mm isotropic resolution, acceleration factor of 2, scan time ~6 minutes.

**Functional image acquisition** Multiband T2\*-weighted images will be acquired during resting state and NF runs with the following parameters: acceleration factor=4, 68 transverse slices, TR=1.2 sec, TE=30 ms, Flip=61°, 2 mm isotropic resolution, field of view=256 mm (optimized in prior NF work). During resting state runs (~10 mins), subjects will view a central fixation cross and will be instructed to let their minds wander. During NF runs (six runs of ~2.5 minutes each), subjects will be prompted to follow the mindfulness instructions.

